### Design

2.1.

The study is a parallel group, cluster-randomized controlled superiority trial. Schools will be chosen as the unit of randomization to minimize contamination effects and to follow the municipality’s chosen strategy for implementation. This chosen strategy implements GBG in all K–3 (typically corresponding to children aged 6–9) classrooms simultaneously in every included school, rather than allowing for implementation in single classrooms in different schools. The group ratio will be 1:1 and randomization will be stratified using an aggregated sociodemographic index score used by the municipality to allocate school funding.

As the study and intervention lasts for a Swedish school year (August to June the following year) randomization will be conducted in May, before the end of the preceding school year. This is to ensure that schools have a similar amount of time to prepare for GBG as corresponding to their usual practice, as well as allowing the research group time to prepare all schools for data collection procedures. Randomization will be conducted and implemented by the research team. After recruitment all schools will be stratified as higher or lower than the city average on the stratification variable, i.e., the municipality’s sociodemographic index score, which has a centered mean at 100. Following this procedure, schools will be assigned a computer-generated number between 0 and 1 using the statistical software SPSS (RRID:SCR_002865), where schools with the highest numbers in each stratum will be placed in the intervention group. The research group will then notify schools of their study allocation, which will either be the intervention group who will receive training in GBG, or the control group, who will be conducting BAU. Schools in the control arm will be offered GBG-training in the following school year as an incentive to participate. GBG will be conducted by teachers who receive training during the study from certified GBG-trainers provided by the municipality.

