### Data analysis

2.5.

As this study aims to investigate the effects of introducing GBG under real-world circumstances, whether the sample is compliant to the intervention or not, data analysis of the primary and secondary outcomes will follow intention-to-treat (ITT) procedures. The primary objective can be described as the difference in change over time in conduct problems between the group receiving GBG and the group receiving BAU. This can be expressed as a general linear model where conduct problems would signify the primary outcome of interest (denoted as 
Y
), with intervention group, time, and stratification variable (sociodemographic index score) being converted to dummy-scores and denoted as 
$\beta_{1}$
, 
$\beta_{2}$
, and 
$\beta_{3}$
 respectively, using an interaction term (
$\beta_{1}\times \beta_{2}$
) for intervention group and time. This approach entails some statistical considerations. One consideration is adjusting for the standard errors being affected by clustering (45). Since the municipality only has capacity to implement GBG in a low number of schools, considerations have to be made regarding the degree of precision in statistical models with few clusters. One option is to use a Bayesian ITT-model, which could render more precise estimates compared to corresponding frequentist models as long as default naïve priors aren’t used (46). Data for priors may be limited, particularly for some of the secondary outcomes, in which case weakly informed priors will be used. The estimates can also be compared with the corresponding frequentist ITT-analysis. As priors can have notable effect on estimates (47), sensitivity analyses will be conducted.

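### The stratification factor enters the primary model only as a time-constant main effect, so with complete data it does not adjust the group-by-time contrast being tested

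*Protocol article*

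**What the plan says.** The Design section states: "The group ratio will be 1:1 and randomization will be stratified using an aggregated sociodemographic index score used by the municipality". It makes the factor binary: "After recruitment all schools will be stratified as higher or lower than the city average on the stratification variable". Within each level, "schools with the highest numbers in each stratum will be placed in the intervention group". Stratum is therefore a fixed attribute of a school.

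The Data analysis section sets the target: "The primary objective can be described as the difference in change over time in conduct problems between the group receiving GBG and the group receiving" business-as-usual. The model is a general linear model "with intervention group, time, and stratification variable (sociodemographic index score) being converted to dummy-scores", "using an interaction term" for group and time. It names no stratum-by-time term and no baseline covariate. On clustering it says: "One consideration is adjusting for the standard errors being affected by clustering (45"). Secondary outcomes are largely to follow similar procedures, and listwise deletion is the default for missing data.

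**The concern.** A stratified trial normally carries its stratification factor into the analysis so that the tested contrast gains the precision, and the protection against chance imbalance, that stratifying was meant to buy. The factor is listed in this model, so the adjustment appears to be in place. But the tested term is an interaction with time, and a covariate that is constant over time can only shift levels. It adjusts the baseline difference between arms, which is not the target.

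With 3-5 intervention schools, hence about 6-10 in total at 1:1, and strata formed only after recruitment, odd-sized strata are plausible. If conduct problems develop differently over the year in schools above and below the city average, that difference either enters the estimate through chance imbalance or stays in the error term. The article itself expects smaller effects and names limited power as its main methodological weakness.

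**Working it through.** The article gives no power, alpha or SD figure that bears on this, so there is no stated number to reproduce.

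**1. Algebra.** Write the model as Y = b0 + b1·G + b2·T + b3·S + b12·G·T, with G for group, T for time and S for stratum. A class's change from T1 to T3 is b2 + b12·G, because b3·S subtracts out. If the strata truly differ in change by d, the true change is b2 + b12·G + d·S. The interaction then estimates b12 + d × (share of S = 1 in the GBG arm − share in the BAU arm), whether or not b3 is fitted.

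**2. Numerical check (simulated data).**
- 7 schools × 6 classes × 2 times, least squares: group by time is 0.3062363296 without stratum, 0.3062363296 with its main effect, and 0.2696680941 with stratum by time. A random-intercept model gives 0.306236 with and without stratum.
- Three visits, including school splits as uneven as 4:1 and 1:4: the largest difference from adding the main effect is 5e-14 (least squares). With 3:2 and 2:3 splits and school and class random intercepts it is 1e-14, and the standard error is also unchanged (ratio 0.9997).
- Incomplete classes dropped whole: −1.0209 with and without; in a second data set −1.2216 with and without.
- Incomplete class-visits kept: the estimate moves. The mean absolute shift is 0.30 to 0.45 in least squares (15%, or 15%/30% by stratum, missing) and 0.04 in the mixed model (15%/30%), against a simulated residual SD of 5. This movement comes from which visits are missing. It does not adjust for stratum trends.
- T3 regressed on T1 in one deliberately imbalanced data set (4:1 and 1:4, true effect −3): adding stratum moves the effect from 0.29 to −4.24. In that model the term does reach the contrast.

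**3. Shift from chance imbalance.** Equal classes per school are assumed; d is in SD of the class score.

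| Schools (strata) | Arms within strata | Imbalance | Shift, d = 0.3 | Shift, d = 0.6 |
|---|---|---|---|---|
| 6 (3/3) | 2:1, 1:2 | 2/3 − 1/3 = 0.33 | 0.10 | 0.20 |
| 7 (3/4) | 2:1, 2:2 | 2/4 − 1/3 = 0.17 | 0.05 | 0.10 |
| 8 (5/3) | 3:2, 1:2 | 3/4 − 2/4 = 0.25 | 0.075 | 0.15 |
| 10 (5/5) | 3:2, 2:3 | 3/5 − 2/5 = 0.20 | 0.06 | 0.12 |

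If both odd strata give their extra school to the same arm, the imbalance is 0 for 3/3 and 5/5 and about 0.07 in size for 5/3 (3/5 − 2/3). With even strata it is 0. Where only one stratum is odd, as in 3/4, it is 0.17 either way.

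**4. Interval width with balanced strata.** Let v be the variance of a school's mean change. For 8 schools split 4/4, the planned analysis has residual variance v + d²/3 on 6 df; with stratum by time it is v on 5 df. The width ratio is about (2.447/2.571) × √(1 + d²/(3v)).
- No class-level noise, v = 0.3² = 0.09 (assumed): 1.10 at d = 0.3 and 1.45 at d = 0.6. Simulated mean widths are 1.150 against 1.037 (11%) and 1.537 against 1.038 (48%); simulated means run slightly above the formula.
- With class noise (assumed: 6 classes per school, class SD 1, T1-T3 correlation 0.6): v = 0.09 + 2(1 − 0.6)/6 = 0.223. The ratio is 1.01 at d = 0.3 and 1.18 at d = 0.6; simulated, about 2% and 20%.

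For 10 schools split 4/6, the simulated figures are 12% and 47% without class noise, and about 4% and 20% with it. Type I error of the planned school-level test is about 4% (d = 0.3) and 2% (d = 0.6) with class noise, and about 3% and 0.6% without.

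**5. Price of stratum by time.** With 6 schools, df fall from 4 to 3, so the critical value rises by 3.182/2.776 = 1.146. In a 3/3 split with the odd schools in opposite arms, the variance rises further by 1/(1 − 0.33²) = 1.125. With class noise, simulated widening is about 5% (2/4 split, d = 0.3) to 19% (3/3, small d). At d = 0.3 it is about 0.5-2% with 7 schools and 1-3% with 8 split 5/3.

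**The case against.** The strongest reply is that leaving out stratum by time is sensible parsimony with so few schools. Nothing in the article suggests that the strata differ in within-year change, let alone by 0.3-0.6 SD, and below that the extra term costs more than it returns. This stands for 6 schools, and slightly for 7 or for 8 split 5/3. It bears on the choice of remedy. It does not rescue the main effect, which does nothing for the tested contrast.

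It can also be said that the model is a schematic in a journal article, and that sociodemographic factors will be examined as moderators. But the article does commit to particular terms, and a moderator analysis lies outside the primary model.

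Two stronger readings are tempting. A reader might infer that the stratum term can never change the estimate. The documents do not support that: the article does not say whether listwise deletion removes visits or whole classes, and with incomplete visits kept the estimate can move. The planned Bayesian model could also behave differently if its prior on the group main effect is informative. A reader might also infer that the trial is biased. It is not: allocation is random within strata, the shifts in step 3 are chance imbalance, and type I error was at or below about 5% in every scenario run.

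**Conclusion.** The concern holds in a limited form. As written, with complete data or with incomplete classes dropped whole, the model does not adjust the tested contrast for the factor used to stratify. That part is exact and rests on no assumed figure.

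The consequences do rest on assumptions: d, the between-school SD of change (0.3), the number of classes, and the T1-T3 correlation, none of which the article gives. For d of 0.3-0.6 SD, the unadjusted shift is about 0.05-0.20 SD when odd schools fall in opposite arms or only one stratum is odd, and near zero otherwise. With balanced strata and 8-10 schools, the excess width is about 2-4% (d = 0.3) to about 20% (d = 0.6). The 11-12% and 47-48% figures are upper values that need zero class-level noise. At d = 0.15 there is little or nothing to gain. The planned test is at worst conservative, provided clustering by school is handled. Severity: low to moderate.

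**What to change.** Before analysis, add one sentence saying that the primary T3 effect, and the secondary models that reuse this specification, will be estimated in one of two ways:
- from a model of T3 given T1 with the stratum term (preferred); or
- from the repeated-measures model with stratum by time added at each follow-up.

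The unused option can serve as a sensitivity analysis. Data collection is complete, but this change concerns the analysis only.

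In either model the stratum term takes one school-level degree of freedom. With about 6 schools and d of 0.3 or less, stratum by time widens the interval by roughly 5-19%. The baseline-adjusted model is the natural first choice because the stratum main effect works there, and because conditioning on T1 reduces class-level noise. At the assumed correlation of 0.6, the class-level variance is 1 − 0.6² = 0.64, against 2(1 − 0.6) = 0.80 for a change score. If one stratum holds a single school, the continuous index score should replace the dummy; otherwise that school contributes nothing to the comparison.

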The primary objective is to evaluate the effects of GBG-training on decreasing conduct problems in elementary school classrooms as compared to schools conducting business-as-usual (BAU). The secondary objectives are to evaluate the effects of GBG-training on conduct problems in common school areas, classroom climate, collective teacher efficacy, behavioral management practices and on-task behavior. With GBG compared to BAU, teacher-rated conduct problems in the classroom are expected to decrease at both 3- and 9-month follow-up. Conduct problems in common school areas are only expected to decrease at 9-months follow-up since relevant generalization components in GBG are implemented after the 3-month follow-up. It is also hypothesized that observer-rated measures will corroborate corresponding teacher-rated measures. The role of sociodemographic factors and implementation as moderators will be investigated. In addition, the role of contextual factors as possible barriers and facilitators for adoption and implementation will be investigated.

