#### Teacher-rated measures

2.4.1.

One teacher from each included class will respond to a demographic questionnaire developed for the trial concerning the number of students in each class, number of boys (to assess gender distribution), number of students where Swedish is a secondary language, number of students (partially or wholly) excluded from ordinary classroom activities, additional staff in the classroom, and experience with the current class. Demographic items are assessed at T1 and T3. The intervention group receives two additional items at T3 regarding the number of GBG-sessions they had the previous week and if they expect that they will continue using GBG during the next school year.

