#### Fidelity

2.4.3.

Certified trainers in GBG observe teachers in the experimental group on nine occasions, three for every phase in GBG, during the school year. The trainers rate procedural fidelity at each observation, before, during, and after the GBG-session using a standardized form. Scores will be averaged for the observation sessions to create a score for procedural fidelity.

Due to previous difficulties, collecting data on dosage (e.g., frequency and duration of GBG-sessions) is no longer a part of the trainer’s usual practice. To ensure that there is some proxy for dosage, trainers are asked to collect data on dosage through a weekly chart that tracks whether the teacher has played GBG 3 times during the week or not. Further measures regarding dosage have not been judged as feasible.

Trainers may certify teachers at the end of the school year. The requirements for certification in GBG are participation in all three training sessions, conducting at least 60 GBG-sessions during the school year, being observed by a certified trainer at least nine times and judged to conduct sessions with enough fidelity. This will constitute a binary variable, serving as a general measure for what the trainers assess as being passable implementation quality, to complement procedural fidelity.

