Analyses for secondary outcomes, including observational measures, will in large follow similar procedures, i.e., as outcomes in linear univariate models. Statistical analyses related to implementation will be treated differently. To assess implementation as a moderator, a parameter for procedural fidelity will be added to the statistical model for the primary analysis. Note that this is contingent on the chosen proxy for implementation to have some degree of variation. An earlier study reported high procedural fidelity across the board, with only dosage being suboptimal (21). This indicates that dosage may be a more potent moderator to investigate compared to procedural fidelity. Due to the previously mentioned difficulties in collecting data on dosage, the teacher-rated variable for number of GBG-sessions last week may be used as a proxy for dosage instead of the trainer-collected data on number of GBG-sessions for the school year.

While all data collection is handled by employees who have the same or similar formal requirements, the theoretical requirements of data “missing completely at random” are high. It is also possible that data could be “missing at random”, but in this case there are many unobserved variables that could potentially explain systematic differences between missing and observed data. Should missing data occur, it will primarily be assumed as “missing not at random”. Consequently, listwise deletion will be the default option to handle missing data. Multiple imputation will also be considered in cases where arguments can be made for data being missing at random, or where inclusion of auxiliary variables is deemed suitable. However, no measured variables in this study are currently expected to predict or correlate with potential missing data.

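### Adding procedural fidelity to the two-arm primary model cannot test implementation as a moderator, because fidelity and every dosage proxy exist only in the GBG arm and only after randomisation

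*Protocol article*

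**What the plan says.** The Introduction of the protocol article states the aim: "The role of sociodemographic factors and implementation as moderators will be investigated". Section 2.5 (Data analysis) gives the method: "To assess implementation as a moderator, a parameter for procedural fidelity will be added to the statistical model for the primary analysis". The model referred to is two-arm. It has dummies for group, time and sociodemographic stratum plus group × time, and its target is the "difference in change over time in conduct problems between the group receiving GBG and the group receiving BAU".

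The implementation variables come from one arm:

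- **Procedural fidelity** (section 2.4.3): "Certified trainers in GBG observe teachers in the experimental group on nine occasions, three for every phase in GBG, during the school year". "Scores will be averaged for the observation sessions to create a score for procedural fidelity".
- **Weekly session chart and certification** (section 2.4.3): both describe teachers trained in GBG.
- **Sessions last week**, the substitute dosage proxy (section 2.4.1): "The intervention group receives two additional items at T3 regarding the number of GBG-sessions they had the previous week".

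The only condition section 2.5 attaches is that the proxy must vary. It gives no value for BAU classrooms and no interaction with time. On missing data it says: "Consequently, listwise deletion will be the default option to handle missing data".

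**The concern.** A moderator of the GBG-versus-BAU effect has to be defined in both arms, and preferably fixed before randomisation, so that the treatment contrast can be compared at different values of it. Fidelity meets neither requirement. BAU teachers have no GBG session to rate, and the score accumulates over the school year in which the outcome is measured. A class that is becoming easier to manage may produce both better fidelity ratings and fewer conduct problems.

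At stake is a stated aim. The planned analysis would yield a coefficient that invites the reading that GBG works better where it is implemented better, when the model does not estimate that. Implementation results are to have their own manuscript (section 4), so the coefficient would probably be prominent there.

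**Working it through.** The plan gives no figure to reproduce, so the check is what the stated model can identify.

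**Model.** With G = GBG, S = stratum, T2 and T3 = follow-up dummies (three time points taken as two dummies) and F = classroom fidelity:

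Y = b0 + b1·G + b2·T2 + b3·T3 + b4·S + b5·G·T2 + b6·G·T3 + b7·F (8 columns).

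An interaction version adds b8·F·T2 + b9·F·T3 (10 columns).

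**Reading 1: F blank in BAU, listwise deletion.** Only GBG rows remain. There G equals the intercept, G·T2 equals T2 and G·T3 equals T3, so three columns are redundant. The rank is 8 − 3 = 5 of 8, or 10 − 3 = 7 of 10. Neither b1 nor b5 and b6 can be estimated. With 3–5 GBG schools (section 2.2) and 1:1 allocation (section 2.1), the loss is 3–5 of 6–10 schools. A numerical rank check gave the same ranks. It assumed 8 classes per school, with 72 of 144 rows left at 3 schools per arm and 120 of 240 at 5. The ranks do not depend on those assumptions, provided F varies between GBG classes.

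**Reading 2: F = 0 in BAU, one additive parameter.** The rank is 8 of 8, so the model can be fitted. The between-arm difference in change to T3 is b6, which does not contain F. Moderation of the change is thus zero by construction, and b7 only shifts the GBG level by the same amount at T1, T2 and T3. T1 is measured before training starts (section 2.1), when no fidelity exists.

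**Reading 3: F = 0 in BAU, with F × time.** The rank is 10 of 10. The difference in change to T3 is b6 + b9·F. Because F is 0 throughout BAU, F is identical to G·F and b9 is estimated from GBG classrooms alone. With raw coding, b6 is the effect at fidelity 0, outside the likely range. With F centred at the GBG mean, b6 is the effect at average fidelity.

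**Size under reading 3.** An illustrative simulation used ordinary least squares and 500 runs. All inputs are assumed: 4 schools per arm, 8 classes each, baseline and one follow-up, fidelity mean 0.8 and SD 0.1, true group × time effect −3, and no true moderation.

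| Fidelity and class trajectory | Coding | Group × time, mean (SD) | Fidelity × time, mean (SD) |
|---|---|---|---|
| Unrelated | raw 0 | −3.05 (7.34) | 0.03 (9.01) |
| Unrelated | centred | −3.03 (1.20) | −0.33 (8.47) |
| Correlation 0.5 | raw 0 | 4.87 (6.62) | −9.92 (8.19) |
| Correlation 0.5 | centred | −3.01 (1.17) | −10.51 (8.18) |

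These agree with theory.

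- In the unrelated case, the raw-coded SD should be about √(1.20² + 0.8² × 9.01²) = 7.3.
- In the correlated case, the trajectory contributes −2 per unit of a standard normal variable, so the spurious slope is −2 × 0.5 × 0.1 / 0.1² = −10. Raw coding then gives group × time of −3 + 0.8 × 10 = +5.

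Centring repairs group × time but leaves the spurious slope. The additive model of reading 2 kept group × time between −2.88 and −3.08 in all four settings, so it does no harm to that estimate but says nothing about moderation.

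**The plan's caveat.** Requiring variation guards against a different failure. If F is the same in every GBG class, it is a multiple of G and the rank is 7 of 8. The absence of control-arm values is not covered.

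**The case against.** **The model can be fitted.** A reader might infer that the planned model cannot be estimated at all. The article does not support that: certification and session counts have a natural value of 0 in untrained schools, and with 0 coding the design has full rank. This stands. The fault lies in what the coefficient means.

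**Losing the control arm is only one reading.** The missing-data paragraph concerns values that were meant to be collected, whereas fidelity in BAU is not applicable. The article nowhere says that controls would be deleted. This also stands. Reading 1 is a possible consequence, and the conclusion does not depend on it because readings 2 and 3 fail too.

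**Collinearity.** A reader might infer that 0-coded fidelity nearly duplicates the arm indicator and ruins the treatment estimate. With equal arms the variance inflation factor is 1 + m²/(2s²) for fidelity mean m and SD s. That is 1 + 0.81/0.005 = 163 at 0.90 and 0.05, and 1 + 0.64/0.02 = 33 at 0.80 and 0.10. The article gives no fidelity scale or distribution, so no single figure can be defended. The inflation also concerns the group main effect under raw coding, not group × time in the additive model.

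**An article condenses.** Coding, centring and interactions may be set out in the full protocol or the analysis plan, and section 2.5 does say that implementation analyses will be handled separately. Missing detail alone would be no finding. But the section names the model and the term to be added, and no coding of that term makes it a test of moderation.

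**Conclusion.** The point holds as a moderate defect in a secondary analysis. The stated analysis cannot answer the stated aim of examining implementation as a moderator. Depending on how BAU is handled, it loses the control arm, estimates a constant GBG level shift, or estimates a non-randomised association within GBG. That conclusion follows from the model's structure and from where the data are collected. It needs only that fidelity varies between GBG classrooms.

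The simulated sizes (SD 7.3 against 1.2, a spurious slope near −10) rest on assumed class numbers, variances and fidelity distribution, and serve only as illustration. The primary intention-to-treat comparison is untouched, and nothing here should be read as a criticism of it.

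**What to change.** Replace the sentence in section 2.5 before analysis begins:

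- **Main replacement.** An exploratory model in GBG classrooms only: T3 conduct problems on classroom fidelity (or dosage), adjusted for T1 score and stratum and allowing for school clustering. Report it as an association and not as moderation of the trial effect.
- **If a two-arm model is kept.** Centre fidelity within GBG, set BAU to 0, cross it with time, and interpret the fidelity × time term in the same associational way.
- **Terminology.** Reserve moderator for variables defined in both arms, such as the sociodemographic stratum.

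A complier-average analysis with certification as the exposure is not a good substitute. It requires allocation to act only through certification. Under section 2.4.3, certification needs all three training sessions, at least 60 GBG sessions, nine observations and a favourable judgement of fidelity, so an uncertified teacher may still have delivered a good deal of GBG.

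The cost is wording and one small model, with no new data. The drawback is that the within-arm analysis rests on 3–5 schools, so it will be imprecise and must be labelled exploratory.

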Game time does not necessarily increase during the generalization phase, instead focus is placed on incorporating components of GBG outside the specified game time. For example, the generalization component of this phase may entail teachers still referring to three rules and delivering praise contingent on adhering to the rules, while maintaining a 4:1 praise-to-reprimand ratio. At the same time, the teacher should remove the usage of teams, their respective posters, and their point cards. At first, this method of generalization is only used for about 5 min immediately following a regular game session. As the phase progresses, it is conducted during longer periods of time, and not necessarily as a direct extension of a regular game session. Teachers are also prompted to have students discuss and share reflections regarding the game once in a while during this phase.

The number of game sessions is set to 3 times a week during all phases. This default format is designed to last for a school year with a class that is naïve to GBG, which is the focus of this study. Teachers may start the school year in a later phase when conducting GBG with students who already have experience with GBG.

Although this Swedish adaptation keeps GBG within the classroom environment, the municipality uses a school-wide implementation process, meaning all K–3 teachers within a school are required to receive training and implement the intervention simultaneously. Teachers receive about 3.5 h of group instruction prior to every phase. The trainers also observe the teachers approximately once per month (nine times in total during the school year), using a standardized form, and delivering feedback to the teacher after every observation.

All training in GBG is conducted by certified trainers in GBG employed by the municipality. The standard path to becoming certified as a GBG-trainer is by first becoming certified in conducting GBG in the classroom. After this, a person can be certified as an internal GBG-coach by observing and giving feedback on procedural fidelity at least twice in all three phases, accompanied by a certified trainer. The final step is to conduct training sessions together with certified trainers during a year of implementation before becoming a certified GBG-trainer, making the entire process approximately three years long.

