##### Conduct problems

2.4.1.1.

The primary outcome for this study is conduct problems in the classroom. This will be measured using the scale “Problem Behavior in the Classroom Last Week,” listing 20 items concerning conduct problems commonly found in school classrooms, e.g., verbal assault directed towards other students, disturbing or distracting other students, and physically assaulting other students. A secondary outcome is conduct problems in school environments, which will be measured using the scale “Problem Behavior in the School Environment Last Week.” The scale remains similar to its classroom counterpart and consists of 15 items concerning conduct problems experienced in school common areas. For both scales, the teacher bases their ratings on the week prior to assessment and rates all items on a scale from 0 (no times last week) to 4 (several times a day). Both scales were translated from Norwegian to Swedish and have shown sound psychometric properties in previous Norwegian studies, with internal consistency at α = 0.88 and α = 0.84 for the respective classroom and school environment scales (37–39). Conduct problems will be assessed at all three time points.

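### Section 2.5 calls a year-long session count what Section 2.4.3 describes as a weekly yes/no chart, and lets a one-week T3 teacher item replace it, so a dosage association could be biased in either direction

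*Protocol article*

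**What the plan says.** All places are in the protocol article.

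- **What trainers record (2.4.3, Fidelity).** Dosage is tracked through "a weekly chart that tracks whether the teacher has played GBG 3 times during the week or not". The section adds: "Further measures regarding dosage have not been judged as feasible".
- **How the analysis section describes that source (2.5, Data analysis).** It is "trainer-collected data on number of GBG-sessions for the school year".
- **The permitted substitute (2.5).** The teacher-rated "number of GBG-sessions last week may be used as a proxy for dosage instead of the trainer-collected data on number of GBG-sessions". The reason given is the earlier difficulty in collecting dosage data.
- **When the substitute is collected (2.4.1, Teacher-rated measures).** The intervention group alone receives "two additional items at T3 regarding the number of GBG-sessions they had the previous week" and continued use. The item is asked once.
- **What the primary outcome covers (2.4.1.1, Conduct problems).** On this scale "the teacher bases their ratings on the week prior to assessment".
- **Planned frequency (2.3, Interventional methods).** "The number of game sessions is set to 3 times a week during all phases".
- **A rule that presupposes a count (2.4.3).** Certification requires, among other things, "conducting at least 60 GBG-sessions during the school year".

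The moderator that Section 2.5 actually enters in the model is procedural fidelity. Dosage is then raised as possibly the more potent one.

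**The concern.** There are two linked problems.

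First, Sections 2.4.3 and 2.5 describe the same source in incompatible terms. An analyst following 2.5 would look for a year total that the measurement section does not describe.

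Second, Section 2.5 lets a source spanning the year be replaced by a report on one week at its end. Exposure and outcome would then come from the same unblinded teacher and essentially the same week. A calm week may leave room for more sessions. A disruptive week may crowd sessions out, or may prompt the teacher to hold more of them. Each mechanism links the one-week count to the T3 rating without any effect of cumulative dose.

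Implementation as a moderator is a stated objective in the Introduction, and Section 4 plans a separate manuscript on implementation. Data collection is complete (Section 5), so the choice between the two variables should be settled before results are seen.

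**Working it through.** The article gives no reliability, power or effect figure for dosage, so there is nothing of its own to reproduce. Three checks were made.

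**1. Can the chart yield a session count?**

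Inputs: three sessions per week (2.3) and a yes/no entry per week (2.4.3). Assumed: W = 30 to 40 teaching weeks, a yes meaning exactly three sessions and a no meaning zero to two.

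With y yes weeks, the total lies between 3y and 3y + 2(W - y).

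- y = 0: 0 to 60 sessions (W = 30), 0 to 72 (W = 36), 0 to 80 (W = 40).
- y = 18, W = 36: 54 to 54 + 36 = 90 sessions, which straddles the 60 in the certification rule.
- Two sessions every week for 36 weeks gives 72 sessions and no yes week.

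The chart alone therefore cannot supply the number that 2.5 mentions.

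**2. How well does each measure track the yearly dose, if weekly variation is pure noise?**

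Model A (assumed): weekly count Binomial(3, p), with p following a Beta distribution across teachers (mean 0.6 or 0.8, concentration c = 1, 3 or 8) over 36 weeks. The correlation between two weeks of the same teacher is 3/(3 + c). The slope multiplier for the one-week count is 3/(3 + c) + [1 - 3/(3 + c)]/36, and its correlation with the yearly mean is the square root of that.

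| c | 3/(3 + c) | Slope multiplier | Correlation with year |
|---|---|---|---|
| 1 | 0.75 | 0.75 + 0.25/36 = 0.76 | 0.87 |
| 3 | 0.50 | 0.50 + 0.50/36 = 0.51 | 0.72 |
| 8 | 0.27 | 0.27 + 0.73/36 = 0.29 | 0.54 |

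In simulation, the number of yes weeks correlated 0.86-0.94 with the yearly total. That run drew the yes weeks separately from the sessions counted, so it somewhat understates the chart.

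Model B (assumed): mean 2.2 sessions per week, between-teacher SD 0.4-0.8, week-to-week SD 0.8-1.2, rounded counts from 0 to 5, 36 weeks. The last-week count correlated about 0.35-0.70 with the yearly mean, a slope multiplier of 0.12-0.48. The share of weeks with at least three sessions correlated 0.95-0.98. With only 4 charted weeks, the share still reached 0.52-0.81, against 0.35-0.69 for the last week.

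**3. What if that week's deviation is related to the outcome?**

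Let D be the true dose (variance 1) and R the reliability of the one-week count. Let X = D + sqrt((1 - R)/R) u and Y = -0.30 D + e, where u and e have variance 1 and correlation r. The slope of Y on X is then

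-0.30 R + r sqrt(R(1 - R)).

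| R | r = -0.5 | r = 0 | r = +0.5 |
|---|---|---|---|
| 0.3 | -0.09 - 0.23 = -0.32 | -0.09 | -0.09 + 0.23 = +0.14 |
| 0.5 | -0.15 - 0.25 = -0.40 | -0.15 | -0.15 + 0.25 = +0.10 |
| 0.7 | -0.21 - 0.23 = -0.44 | -0.21 | -0.21 + 0.23 = +0.02 |

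The true slope of -0.30 can look shrunken, inflated or reversed. The values of R, r and the slope are illustrative; the article gives none of them.

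**The case against.** The strongest reply is that nothing is fixed. Section 2.5 says only that the item may be used, dosage itself is only suggested as a moderator, and the choice of proxy for a secondary analysis may stand in a fuller plan. The article openly calls its dosage data a proxy and explains why. This lowers the weight of the point. It does not remove the mismatch between 2.4.3 and 2.5, which is in the text shown.

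A second reply is that the chart's advantage depends on its being filled in. Section 2.4.3 says trainers are asked to keep it, and Section 5 says data collection is complete; neither says the charts are. This stands. With sparse charts the advantage narrows, and under Model A with the widest spread between teachers it all but disappears at four charted weeks. The chart is still not a rating by the teacher about the outcome week.

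A third reply is that the two teacher reports need not cover exactly the same days, since each collection period runs three weeks. That is fair, and is why the recall week is called essentially the same.

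Three stronger readings are tempting, and the documents do not support them:

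- **That a real dose effect will be attenuated.** This needs weekly error unrelated to the outcome, which the shared week and rater put in doubt.
- **That no session count exists.** The 60-session certification rule leaves open that trainers hold some count, although its collection is not described.
- **That the certification variable is invalid.** It is offered as a general measure of what trainers judge passable, to complement procedural fidelity. It is not offered as a dosage measure, and the article gives no rate of missed visits from which to size a problem.

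**Conclusion.** The point holds as a limited one. Sections 2.4.3 and 2.5 disagree on what the trainer dosage data are and must be reconciled. If the one-week T3 item is used instead, its association with the T3 outcome could be biased in either direction and could not be read as an effect of dose.

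How large the bias would be cannot be derived from the article. Under the stated assumptions, pure noise multiplies the slope by 0.12-0.76 across the two models, and correlated error moves a true -0.30 to between -0.44 and +0.14. Over 36 complete chart weeks, both models rank the chart above the one-week item. How far that carries over depends on chart completeness, which is unknown.

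Only the implementation-moderator analysis is affected. The intention-to-treat comparison on the primary outcome does not use either dosage variable.

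**What to change.** In Section 2.5:

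1. Replace the reference to a yearly number of sessions with a description that matches 2.4.3: the proportion of charted weeks between T1 and T3 in which the three-session target was recorded as met. If trainers do hold a session count, for instance for certification, describe in 2.4.3 how it is obtained.
2. Name that proportion as the main dosage variable, and report the number of weeks charted for each class.
3. Use the T3 last-week item only in a separate sensitivity analysis, with a stated caution about the shared week and rater. Do not use it to fill in the chart variable for some classes, because that would put two scales into one variable.

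The cost is wording only, provided the charts were kept as 2.4.3 describes; no new data are needed. The downside is that incomplete charts make the measure less precise, which the reported number of weeks will show.
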